## Methods/design

### Study design and setting

This study is multicenter clinical superiority parallel-group randomized controlled trial, designed according to the SPIRIT 2013 checklist (Additional file 1). The final study protocol version 6.0, December 2021, was approved by the Ethics Committee of Arnhem-Nijmegen in the Netherlands (NL 78403.091.21) and registered in ISRCTN44345202 (March 2022).

Participating centers in the Netherlands are the Wilhelmina Children’s Hospital in Utrecht, the Radboudumc Amalia Children’s Hospital in Nijmegen, Isala Clinic in Zwolle, and TOP voor kinderen in Arnhem. The first two are academic referral centers, the latter peripheral centers. The study will be conducted from June 2021 to June 2025. First-, second-, and third-line centers are participating in this study with the intention to select not only therapy-resistant children referred to third-line centers but also children seeking medical attention for functional DUI at the start of their condition.

The study consist of three parallel arms: urotherapy (care as usual), urotherapy with addition of a SENS-U device, and urotherapy with addition of a SHAM device. Outcomes parameters are measured at baseline, after the end of 3-week training with or without SENS-U/SHAM, after 3 months at the end of urotherapy, and 6 months after start of the training. Total study duration is 4 years. Individual study duration for subjects is 6 months.

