### Primary outcomes and secondary outcomes

The main study outcome is the number of wetting accidents per week after 3 months of urotherapy. Secondary outcomes are number of per-post wetting accidents classified further according to the ICCS standards in complete response (100% reduction of complaints), partial response (50-99% reduction), and no response (less than 50% reduction) [14]. Furthermore, magnitude of the placebo-effect contribution (SHAM versus control) will be assessed next to subjective improvement of symptoms according to child and parents, number of wetting accidents per week during follow-up 6 months after baseline, cost effectiveness, and change in FVC parameters (average, minimum, maximum voided volumes corrected for bladder capacity for age (EBC) between baseline (T0), after 3 months (T3), and after 6 months (T6). Change in disease specific quality of life as measured by the PINQ is also compared between T0, T3, and T6.

Other objectives include adherence to urotherapy and adherence of wearing the SENS-U/SHAM, patient experiences of user friendliness/(dis)comfort of the SENS-U/SHAM device, occurrence of urinary tract infections and constipation, and uroflowmetry curves.

Adherence to urotherapy is defined as number of failed contact moments/number of expected contact moments during the 3 months training. The SHAM and SENS-U measure the number of days actually worn. Adherence of wearing the SENS-U/SHAM is measured as a proportion (number of days not worn/total number of days used in training).

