### Sample size

The sample size calculation is based on detecting a difference between the intervention (SENS-U) group and the placebo (SHAM) group at the 3 month endpoint on the primary outcome number of wetting accidents per week. Following the ICCS guidelines, most published studies categorize the number of “wetting accidents per week” in three categories (complete response, partial response, no response) [14]. Information about the initial data used for the categorization (i.e., the number of wetting accidents) is seldom available. Therefore, our sample size calculation is based on a Fisher’s exact test with the known proportions. This will give a slight overestimation of the necessary sample size when analyzing wetting accidents per week, since this latter variable has more variance.

In this calculation, we assume the SHAM condition to be comparable to urotherapy using currently existing wearable alarm treatments (timer watch, pants alarm) [13, 15]. Success rate vary between 53 and 74%, depending on type of referral center [16, 17]. Since this study includes first- to third-line centers, we use an average success rate of 64% to be the estimate success rate of the SHAM condition in our sample size calculation. In addition, we expect at least a 15% additional effect in the intervention (SENS-U) group, based on current clinical experiences with the SENS-U [12].

With a Fisher’s exact test for two independent proportions, one-sided *a* = 0.05, power = 0.80, 64% success in the SHAM group, and 79% success in the SENS-U group, 124 children per group are needed. The one-sided alpha will provide a slight underestimation of the sample size. Given the previous assumption that our sample size calculation result in slight overestimation of the sample size, we presume that the overestimation and underestimation will cancel each other out. With 23% lost to follow-up, we need 160 children per group, 480 children in total.

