### Data analysis and publication

Data are analyzed according to an intention to treat analysis, without replacement of individuals who withdraw during the study, using a Poisson or linear mixed model (depending on the distribution of the main outcome) with all available study time-points used. In case of premature withdrawal, last available data will be used. A correction for baseline, center, age, cumulative dose of antimuscarinics (if applicable), and adherence/drop-out will be performed. A random intercept and slope will be estimated if model fit allows for it. Descriptive statistics are used to analyze subjective improvement according to child and parents, adherence to treatment and to the SENS-U/SHAM device, user friendliness and (dis)comfort of the SENS-U/SHAM, and other previously mentioned outcome objectives. The data generated by the validated PIN-Q and EQ-5D-5L instruments are transformed and interpreted according to instructions given for each questionnaire [18–20]. A mixed model analysis is done to detect any difference in outcome between the three groups. Subgroup analysis will be done to study the effect of treatment in different age-groups, center, gender, socio-economic background, and in case of psychiatric co-morbidity. No interim analysis is done as no significant risks or benefits are expected for one of the three different study groups.

The results are shared with relevant fora and data will be presented at international conferences and published in peer reviewed medical journals without restrictions.

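### The withdrawal rule reads as last observation carried forward, which conflicts with the planned mixed model and the sample size and biases the 3-month endpoint in a direction that cannot be known in advance

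*Protocol article*

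**What the plan says.** All references are to the protocol article.

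- **Data analysis and publication.** The analysis is by intention to treat, "using a Poisson or linear mixed model (depending on the distribution of the main outcome) with all available study time-points used". The next sentence reads: "In case of premature withdrawal, last available data will be used". The one after it adds: "A correction for baseline, center, age, cumulative dose of antimuscarinics (if applicable), and adherence/drop-out will be performed".
- **Primary outcomes and secondary outcomes.** "The main study outcome is the number of wetting accidents per week after 3 months of urotherapy". Response categories are defined by the percentage reduction in complaints.
- **Study design and setting.** "Outcomes parameters are measured at baseline, after the end of 3-week training with or without SENS-U/SHAM, after 3 months at the end of urotherapy", and again at 6 months.
- **Sample size.** The trial is sized for "detecting a difference between the intervention (SENS-U) group and the placebo (SHAM) group at the 3 month endpoint", with 124 evaluable children per group. It is then inflated: "With 23% lost to follow-up, we need 160 children per group, 480 children in total".

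**The concern.** For a child who leaves before month 3, the only values that can be carried are the baseline count or the 3-week count. Under the rule, such a value enters the primary endpoint as though it had been measured at 3 months, so the SENS-U versus SHAM contrast becomes a mixture of time points.

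Two other parts of the plan do not fit this. A mixed model on all observed visits already uses the data of children who leave early. If drop-out depends only on what was observed, it needs no substituted values. The sample size removes the 23% from the denominator, whereas the withdrawal rule puts them back with earlier values.

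At stake is the primary estimate, with up to 23% of its values replaced, and whether the stated 80% power describes the analysis that will be run.

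**Working it through.** **Inputs from the Sample size section:** 64% success with SHAM, 79% with SENS-U, Fisher's exact test, one-sided 0.05, power 0.80, 124 per group, 23% loss, 160 per group.

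**Assumed, because the documents do not give them:** success rates among carried values, when children leave, and drop-out by arm. Ranges are shown.

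**Step 1: the plan's own figure.** The continuity-corrected formula for two proportions, one-sided, gives 124 per group, as stated. Exact one-sided Fisher power by enumeration is 80.6% at 124 per group. Expected completers are 160 × 0.77 = 123.2, and power at 123 is 80.2%. The sizing therefore reproduces if leavers contribute nothing and completers show the full 15 points.

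**Step 2: carry-forward with equal drop-out.** All 160 per group are analysed. Success in each arm is 0.77 × (3-month rate) + 0.23 × (carried rate). If success means a reduction from baseline, a carried baseline count is a 0% reduction and so a failure; the first row therefore uses 0%.

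| Carried success, SHAM / SENS-U | Analysed rates | Difference (points) | Fisher power, n = 160 |
|---|---|---|---|
| 0% / 0% (all baseline) | 49.3% / 60.8% | 11.6 | 63.3% |
| 30% / 30% | 56.2% / 67.7% | 11.6 | 64.2% |
| 50% / 50% | 60.8% / 72.3% | 11.6 | 67.2% |
| 64% / 64% | 64.0% / 75.6% | 11.6 | 69.0% |
| 32% / 39.5% (half the gain) | 56.6% / 69.9% | 13.3 | 76.0% |
| 33% / 48% (full gain) | 56.9% / 71.9% | 15.0 | 85.4% |
| 64% / 79% (full gain) | 64.0% / 79.0% | 15.0 | 89.0% |
| 40% / 65% (early gain larger than at 3 months) | 58.5% / 75.8% | 17.3 | 94.2% |

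With no arm difference among carried values, the effect is 0.77 × 15 = 11.55 points. Power returns to 80% once the carried values differ by about 8 to 12 points, depending on their level. The last row shows the opposite error: if the arms differ by 25 points at 3 weeks and by 15 at 3 months, the analysed difference exceeds the true one.

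**Step 3: unequal drop-out with no true effect** (64% success in both arms, baseline carried, no covariate adjustment).

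- 28% SHAM and 18% SENS-U: 0.72 × 64% = 46.1% against 0.82 × 64% = 52.5%. This is a false difference of 6.4 points, with one-sided rejection of 27.8%.
- 25% and 21%: 48.0% against 50.6%, one-sided rejection 10.1%.
- 23% and 23%: no difference, one-sided rejection 4.2%.

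**The case against.** **The sentence may mean something harmless.** Standing directly after a clause about using every available time point, it could mean only that a withdrawn child's data up to withdrawal stay in the model. That would be acceptable. However, the preceding clause already says so, which would make the sentence redundant, and carry-forward is the more natural reading. If the harmless meaning is intended, rewording settles the matter.

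**A reader might infer that the rule necessarily shrinks the effect and undoes the 80% power.** The documents do not support that. The 3-week value is taken at the end of device use, and the Discussion expects an early gain in complete response with SENS-U. Carrying such values could preserve the contrast, or exaggerate it if benefit fades once the device is removed. The 63% figure needs every leaver to carry a baseline value, and the documents do not say when children leave. On the other side, the Urotherapy section mentions wetting assessment only at baseline, 3 and 6 months, and the 21-day evaluation is described in terms of comfort and ease of use. Many carried values could therefore be baseline ones. Table 1 is not shown, so this stays open.

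**Unequal drop-out is poorly supported for the primary contrast.** This stands. The Discussion speaks of impaired motivation without a device and lower adherence with one, which bears on device versus control. SENS-U and SHAM wearers both have a device, are blinded to which, and get identical instructions. The 28% versus 18% split is an illustration. The planned correction for drop-out, if entered as an indicator, could also absorb the false difference in that simple case. It would not restore a diluted effect, since it leaves the carried values in the contrast.

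**The power figures are a proxy.** This also stands. The 80% belongs to a Fisher test on success; the planned analysis is a Poisson or linear mixed model of counts.

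**Conclusion.** The point holds in a conditional form. As most naturally read, the rule enters earlier counts as observed 3-month values for up to 23% of children, against both the mixed model beside it and the sizing. The resulting bias has no direction that can be known in advance. On the sizing scale with equal drop-out, power runs from about 63-69% (no arm difference among carried values) through about 76% (half the planned gain) to about 85-89% (full gain), against the planned 80%. An early benefit that fades would lead to overstatement.

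These figures rest on assumed success rates among carried values and on all 23% leaving before month 3. The false-positive figure of about 28% rests on an assumed drop-out split as well. The conflict between the passages depends on none of these assumptions, only on the carry-forward reading. The lack of a sensitivity analysis for data missing not at random is not part of the finding, because that is ordinary content for a statistical analysis plan, which is not at hand.

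**What to change.** Delete the sentence, or reword it to say that data observed up to withdrawal remain in the model. State that the primary mixed model is fitted to all observed visits of all randomised children, with nothing carried forward, and that the SENS-U versus SHAM contrast is estimated at 3 months under missing at random. This also removes the conflict with the sample size, which already discounts the 23%.

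The cost is one sentence, with no extra data. Because it changes the primary estimate, it should be settled before unblinding. An optional addition for the statistical analysis plan is one missing-not-at-random sensitivity analysis, for example multiple imputation with a worse outcome after drop-out, varied by arm.

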### Urotherapy/bladder training

All subjects will receive urotherapy which starts with explanation and instructions. These instructions are also handed out in paper. At baseline, uroflowmetry and ultrasound to measure post void residual (PVR) is performed at least twice. Several patient-related outcome measurements (PROMS) are collected: a 48-h frequency voiding chart (FVC), questionnaires (Pediatric Incontinence Quality of Life (PINQ), EQ-5D-Y), and Rome IV criteria. Number and severity of wet days per week is assessed as baseline parameter.

After this, urotherapy is given for 12 consecutive weeks according to ICCS standards [6]. During this practice period, counseling is given at frequent follow-up appointments according to the local protocol in each center (at least two contact moments after intake and before follow-up at 3 months). Medication for constipation, prophylactic antibiotics, or medication to suppress bladder overactivity are continued if applicable. After 3 months of training, the urotherapist evaluates the outcome of training and number and severity of urinary incontinence per week is assessed again. Uroflowmetry and ultrasound for PVR and voiding diary/FVC parameters are collected again, and outcomes are discussed with the child and its parents. Questionnaires (PINQ, EQ-5D-Y) are filled in, and Rome IV criteria are determined.

If continence is not achieved (or not sufficiently) after 3 months, alternative treatments are discussed. Another contact moment is planned 6 months after start of the treatment to re-evaluate the status, assess the number and severity of urinary incontinence, and collection of previous mentioned PROMS. This is the end of the study period for participating subjects.

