This study has several strengths. Children from first-, second-, and third-line centers throughout several areas in the Netherlands are included to represent the overall group of children with functional DUI as much as possible. It is one of the few studies that will give a better insight in adherence of alarm systems used, as current literature concerning this element is sparse. As previously mentioned, trials studying not only the effect but also the cost-effectiveness of certain treatment modalities are essential as overall health costs are increasing. The study also has some potential limitations. Complete blinding of subjects is only possible for those allocated to either a SENS-U or SHAM device. Those allocated to urotherapy alone are not blinded (nor is the urotherapist in this case). As cognitive behavioral treatment is an important part of training, motivation in those not randomized to any type of device might be impaired. Potential discomfort or social embarrassment in those allocated to a SENS-U or SHAM might lead to less adherence and subsequent impact on outcome as well.

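### The intention-to-treat model adjusts for adherence/drop-out, and possibly post-entry antimuscarinic dose, so its treatment coefficients need not be the intention-to-treat effects

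*Protocol article*

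**What the plan says.** Under Data analysis and publication, the protocol article states the principle: "Data are analyzed according to an intention to treat analysis, without replacement of individuals who withdraw during the study". The model is a Poisson or linear mixed model using all time-points. The same paragraph adds "In case of premature withdrawal, last available data will be used" and then "A correction for baseline, center, age, cumulative dose of antimuscarinics (if applicable), and adherence/drop-out will be performed". Nothing confines any of these terms to a secondary or sensitivity analysis.

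Two adherence measures are defined under Primary outcomes and secondary outcomes. One concerns urotherapy: "Adherence to urotherapy is defined as number of failed contact moments/number of expected contact moments during the 3 months training". The other concerns the device: "Adherence of wearing the SENS-U/SHAM is measured as a proportion (number of days not worn/total number of days used in training". The analysis section does not say which of them is the adherence term.

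On drugs, the Urotherapy/bladder training section says: "Medication for constipation, prophylactic antibiotics, or medication to suppress bladder overactivity are continued if applicable". No period is given over which the antimuscarinic dose is cumulated.

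The Discussion says: "Potential discomfort or social embarrassment in those allocated to a SENS-U or SHAM might lead to less adherence and subsequent impact on outcome as well".

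**The concern.** Randomisation balances what exists before allocation. A covariate that arises afterwards can carry part of the treatment's effect, or share unmeasured causes with the outcome. Conditioning on it then removes part of the effect, or creates an association that randomisation had excluded. Adherence and drop-out are of this kind. Cumulative dose is too, if it is counted from entry onwards.

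The main efficacy estimate and the placebo-effect estimate (SHAM versus control) both come from this modelling. Each is labelled intention to treat, but may answer a different question from the one that label promises.

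**Working it through.** **When each covariate is fixed**

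| Covariate | Timing | Basis in the protocol article |
|---|---|---|
| Baseline, centre, age | Before allocation | Centre and age group are also the randomisation strata |
| Urotherapy adherence | After allocation | Counted over the 3 months of training |
| Device-wear adherence | After allocation, device arms only | Counted over the device period |
| Drop-out | After allocation | By its nature |
| Cumulative antimuscarinic dose | Undetermined | Window not stated; existing medication is continued |

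Other treatments may be considered for children still wet at 3 months, and the model also uses the 6-month visit. A dose counted to 6 months could therefore respond to the outcome itself.

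**The plan's own figures, used only to set a scale**

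Inputs from Sample size: 64% and 79% success, one-sided alpha 0.05, power 0.80, 124 per group, 23% loss, 160 per group.

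- Exact one-sided Fisher power at 124 per group is 0.806, so 124 reproduces.
- 124/0.77 = 161.04, against 160 stated (160 × 0.77 = 123.2). 3 × 160 = 480.
- Standardised planned effect: 2(arcsin√0.79 − arcsin√0.64) = 0.335. The simulation used −0.334 SD, where lower means fewer accidents.

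**Bias from adjusting**

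Let T be the arm and M the post-randomisation covariate, scored so that higher is worse (for example non-adherence). Let U be an unmeasured cause of both M and the outcome Y, with unit within-arm variances:

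- M = aT + g₁U + error
- Y = (τ − ab)T + bM + g₂U + error, so that the total effect is τ

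Since E[U | M, T] = g₁(M − aT), the coefficient of T after adjusting for M is τ − a(b + g₁g₂). The bias is −a(b + g₁g₂). It is zero when a = 0, and its sign follows the sign of a.

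The values of a, b, g₁ and g₂ are assumptions; the article gives none. Simulation used 124 per arm and 4,000 runs, with g₁ = g₂ = 0.5 where a shared cause is present.

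| Case | a | Formula | Simulated, adjusted | Rejection rate, unadjusted → adjusted |
|---|---|---|---|---|
| Arm does not shift M (b = 0.3, shared cause) | 0 | −0.334 | −0.333 | 0.838 → 0.938 |
| Mediator only (b = 0.3) | −0.2 | −0.334 + 0.2 × 0.3 = −0.274 | −0.275 | 0.832 → 0.727 |
| Mediator only | −0.4 | −0.334 + 0.4 × 0.3 = −0.214 | −0.218 | 0.847 → 0.545 |
| Mediator and shared cause | −0.2 | −0.334 + 0.2 × 0.55 = −0.224 | −0.224 | 0.850 → 0.680 |
| Mediator and shared cause | −0.4 | −0.334 + 0.4 × 0.55 = −0.114 | −0.116 | 0.844 → 0.284 |
| Mediator and shared cause | +0.2 | −0.334 − 0.2 × 0.55 = −0.444 | −0.445 | 0.843 → 0.995 |
| Mediator and shared cause | +0.4 | −0.334 − 0.4 × 0.55 = −0.554 | −0.553 | 0.838 → 1.000 |
| No effect, shared cause only (b = 0) | +0.2 | −0.2 × 0.25 = −0.050 | −0.050 | 0.049 → 0.108 |
| No effect, shared cause only | +0.4 | −0.4 × 0.25 = −0.100 | −0.098 | 0.048 → 0.200 |
| No effect, shared cause only | −0.4 | +0.4 × 0.25 = +0.100 | +0.098 | 0.058 → 0.008 |

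Unadjusted estimates stayed between −0.332 and −0.339 when the effect was present, and within 0.002 of zero when it was absent.

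**Structure**

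- If the adherence term is device wear, it has no value in the care-as-usual arm. If it is contact moments, it exists in all three arms.
- Both measures put failures in the numerator (failed contacts, days not worn). A value of 10% describes a good adherer.

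**The case against.** The strongest reply concerns the primary contrast. Children are blinded to SENS-U versus SHAM, and the SHAM and its instructions match the SENS-U. The Discussion speaks of both devices together. There may be little difference in adherence between these arms, and with none the bias is zero. This stands. A reader might infer that the SENS-U versus SHAM estimate is biased; the article supports only that it can be. Blinding does not guarantee equality, though: if SENS-U works, early wetting differs between arms, and attendance, withdrawal and medication may follow.

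Three further inferences go too far:

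- That every contested covariate is post-randomisation. This is certain for adherence and drop-out. A dose carried over from before entry would be partly a baseline characteristic.
- That SHAM versus control cannot be estimated. This would follow only if device wear were the adherence term, and contact-based adherence is available in every arm.
- That drop-out can never be a covariate. Children who withdraw contribute earlier visits, and pattern-mixture models use drop-out patterns. Those models average over the patterns to recover an overall effect, which a plain correction does not do.

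The reversed adherence definitions do not add to the bias. Replacing a proportion by its complement flips that covariate's sign and leaves the treatment coefficient unchanged. The formulas are printed, so this is a labelling error.

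**Conclusion.** Wrong as written. A model described as intention to treat should not be corrected for adherence/drop-out, and cumulative antimuscarinic dose belongs in it only if it is confined to the period before randomisation.

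The risk is most direct for SHAM versus control, where the article itself expects allocation to affect adherence and thereby outcome. Even there the direction is open, because the Discussion also fears lower motivation among children given no device. For SENS-U versus SHAM the risk is conditional on the arms differing.

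The size cannot be known from the article. Under the assumed shifts and paths, the bias was 0.06 to 0.22 SD in either direction with an effect present. With no effect, one-sided type I error ran from 0.008 to 0.20 against a nominal 0.05. These figures come from a linear model with invented path strengths. They show that the adjustment cannot be defended as conservative; they do not predict this trial's result.

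**What to change.** 1. In the primary model, adjust only for baseline accidents, centre, age group and, if wanted, antimuscarinic use at baseline. Remove cumulative dose and adherence/drop-out.
2. State how withdrawals are handled once drop-out leaves the model: as missing data, through the mixed-model likelihood on all available time-points, with a sensitivity analysis. Bring the sentence on last available data into line with this.
3. Report adherence descriptively, as already planned, or in a separate analysis labelled as supportive. If it is modelled there, say which of the two measures is meant. If cumulative dose is used there, state its window.
4. Separately, relabel the two measures as non-adherence, or define them as contacts attended/contacts expected and days worn/total days.

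The cost is wording only. No new data are needed, and the sample size is unchanged, since it comes from a two-group Fisher's exact test without covariates.
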